**\*Bleeding**

Classified as Type 0 – 5 according to the following BARC definitions:

**Type 0**: No bleeding

**Type 1**: Bleeding that is not actionable and does not cause the patient to seek unscheduled performance of studies, hospitalization, or treatment by a healthcare professional; may include episodes leading to self-discontinuation of medical therapy by the patient without consulting a healthcare professional

**Type 2 (minor)**: Any overt, actionable sign of hemorrhage (e.g. more bleeding than would be expected for a clinical circumstance, including bleeding found by imaging alone) that does not fit the criteria for Type 3, 4, or 5 but does meet at least one of the following criteria: (1) requiring nonsurgical, medical intervention by a healthcare professional, (2) leading to hospitalization or increased level of care, or (3) prompting evaluation

**Type 3 (major)**:

**Type 3a**:

- Any transfusion with overt bleeding
- Overt bleeding plus a hemoglobin drop of  $\geq 3$  to  $< 5$  g/dL (provided hemoglobin drop is related to bleeding)

**Type 3b**:

- Overt bleeding plus hemoglobin drop  $\geq 5$  g/dL (provided hemoglobin drop is related to bleed)
- Cardiac tamponade
- Bleeding requiring surgical intervention for control (excluding dental/nasal/skin/hemorrhoid)
- Bleeding requiring intravenous vasoactive drugs

**Type 3c:**

- Intracranial hemorrhage including subdural hemorrhages (does not include microbleeds or hemorrhagic transformation, does include intraspinal)
- Subcategories confirmed by autopsy or imaging or lumbar puncture
- Intraocular bleed compromising vision

**Type 4: Coronary artery bypass graft (CABG)–related bleeding:**

- Perioperative intracranial bleeding within 48 hours
- Reoperation after closure of sternotomy for the purpose of controlling bleeding
- Transfusion of  $\geq 5$  units whole blood or packed red blood cells within a 48-hour period (only allogenic transfusions are considered transfusions for CABG-related bleeds)
- Chest tube output  $\geq 2$  L within a 24-hour period

Notes: If a CABG-related bleed is not adjudicated as at least a type 3 severity event, it will not be classified as a bleeding event. If a bleeding event occurs with a clear temporal relationship to CABG (i.e. within a 48-hour timeframe) but does not meet type 4 severity criteria, it will not be classified as a bleeding event.

**Type 5: Fatal bleeding**

Fatal bleeding is bleeding that directly causes death with no other explainable cause.

BARC fatal bleeding is categorized as either definite or probable as follows:

**Type 5a:**

**Probably** fatal bleeding: bleeding that is clinically suspicious as the cause of death, but the bleeding is not directly observed and there is no autopsy or confirmatory imaging

**Type 5b:**

**Definite** fatal bleeding: bleeding that is directly observed (by either clinical specimen [blood, emesis, stool, etc.] or imaging) or confirmed on autopsy

The site of fatal bleeding is specified as intracranial, gastrointestinal, retroperitoneal, pulmonary, pericardial, genitourinary, or other.

Bleeding Academic Research Consortium (BARC) indicates fatal bleeding is meant to capture deaths that are directly due to bleeding with no other cause. The time interval from the bleeding event to the death should be considered with respect to likely causality, but there is no specific time limit proposed. Bleeding that is contributory but not directly causal to death is not classified as fatal bleeding but may be categorized as other forms of bleeding. Bleeding that leads to cessation of antithrombotic or other therapies may be contributory but again would not be classified as fatal bleeding.

**Confirmation of the stroke/TIA diagnosis**

In the event of a stroke/TIA the diagnosis must be confirmed by the following:

- Neurologist or neurosurgical specialist
- Neuroimaging (CT, or MR, and CTA (computed tomography angiography) or MRA (magnetic resonance angiography))

#### Requirements post confirmed stroke/TIA

In order to determine device placement, LAA flow parameters, and clinical outcomes of the stroke/TIA, the following must be completed:

- TOE
- Modified Rankin Scale assessment 90 days following confirmed stroke/TIA

#### Thrombus

If a thrombus is detected post- procedure, complete an Adverse Event eCRF. The following data will be collected on the CRFs:

- Medication regime at time thrombus
- Medication(s) used to treat thrombus
- Imaging performed to monitor thrombus and frequency of monitoring
- Timeframe for resolution

#### **8.1.1 Serious adverse device effect**

A serious adverse device effect is a serious adverse event related to the device or procedure which resulted in any of the consequences characteristic of a serious adverse event, or that might have led to any of these consequences if suitable action had not been taken or intervention had not been made or if circumstances had been less opportune.

#### **8.1.2 Assessing, recording and reporting serious adverse events, serious adverse device effects, and device deficiencies/complaints**

Safety surveillance within this study and the safety reporting performed both by the investigator and Sponsor starts as soon as the dilator/device delivery system has been introduced. The safety surveillance and the safety reporting will continue until the last visit has been performed, the subject is deceased, the subject/investigator concludes their participation into the study or the subject/investigator withdraws the subject from the study.

All serious adverse events (including deaths), serious adverse device effects, and device deficiency information (if applicable) will be collected throughout the clinical study and reported to the Sponsor. Investigators will record all serious adverse events, serious adverse device effects, and deaths on the appropriate eCRF. Device deficiencies will be reported per country reporting timeline requirements to the Sponsor outside of the database on an Event Report Form (**Appendix I**).

For any serious adverse event (including deaths) and any serious adverse device effect, the investigator shall notify the Sponsor immediately of the investigator's awareness of the event and provide the Sponsor with all necessary documentation needed. Device deficiencies will be reported to the Sponsor outside of the database on an Event Report Form (**Appendix I**), as soon as possible after first learning of the event.

Records relating to the subject's subsequent medical course must be maintained and submitted (as applicable) to the Sponsor until the event has subsided or, in case of permanent impairment, until the event stabilizes and the overall clinical outcome has been ascertained. Additional

information may be requested, when required, by the Sponsor in order to support the reporting of serious adverse events to the CEC, regulatory authorities and/or other authorities.

Serious adverse events and serious adverse device effects should be monitored by the investigator until resolved. The status of the subject's condition should be documented at each follow-up visit.

Events reportable to the Sponsor, EC, CAs and regulatory authorities (as applicable) include:

- All serious adverse device effects
- All serious adverse events (including deaths and whether or not the event is considered device or procedure related)
- Device deficiencies (if applicable) that could have led to a serious adverse device effect if either suitable action had not been taken; if intervention had not been made or if circumstances had been less fortunate

The Sponsor will ensure that all events and device deficiencies are reported to the relevant authorities per country specific regulations.

### **8.1.3 Subject death**

All subject deaths with all necessary documentation needed are to be reported to the Sponsor immediately upon the investigator's awareness of the event. The Sponsor must report the death (classified as a serious adverse event) to the NCAs where the study has commenced no later than 2 calendar days after awareness of the event. An Adverse Event eCRF should be completed and include additional detail surrounding the death and cause of death. The principal investigator should also record observed device deficiencies and assessment, if applicable.

## **8.2 Device Deficiency/Complaint Handling**

During the trial, the investigator will be responsible for reporting all device deficiencies per country reporting timeline requirements. A device deficiency is defined as an inadequacy of a medical device with respect to its identity, quality, durability, reliability, safety or performance and includes malfunctions, and inadequate labeling.

If the device deficiency involves a serious adverse event, the investigator shall notify the Sponsor immediately of the investigator's awareness of the event and provide the Sponsor with all necessary documentation needed.

If the device deficiency does not involve a serious adverse event, the principal investigator should notify the SJM Product Surveillance Department by emailing the information about the device deficiency to the local country office or to: [complaints\\[contact]](mailto:[contact]) or calling [name] as soon as possible after becoming aware of the device deficiency. This information will be collected outside of the database on an event report form located in **Appendix I**. The event report form should be completed by a local SJM representative or the investigator. Please contact the local SJM representative to coordinate product returns as applicable.

St. Jude Medical will manage all device deficiencies related to the identity, quality, durability, reliability, safety or performance of the marketed study device and reporting to the appropriate regulatory bodies.

## **9. DATA MANAGEMENT**

Overall, the Sponsor will be responsible for data handling. The Sponsor and/or its affiliates will be responsible for compiling and submitting all required reports to governmental agencies.

Data will be analyzed by the Sponsor and may be transferred to the Sponsor's locations outside of Europe and/or any other worldwide regulatory authority in support of a market-approval application.

St. Jude Medical respects and protects personally identifiable information that is collected or maintained. As part of its commitment, SJM is certified to the U.S. - European Union Framework and U.S. – Swiss Safe Harbor Framework Agreements regarding human resources and subject clinical trial personal information. The privacy of each subject and confidentiality of his/her information will be preserved in reports and when publishing any data. Confidentiality of data will be observed by all parties involved at all times throughout the clinical study. All data will be secured against unauthorized access.

Electronic CRFs will be used in this study, as noted below and in the data management plan. Informed consent documents will be translated to each country's language, as applicable. If additional documentation is required for any reason (e.g. procedural notes for an adverse event), it is to be appropriately redacted/de-identified prior to being sent to SJM. Source documents will be collected and translated, as needed, for CEC meetings, reporting, etc.

The principal investigator or institution will provide direct access to source data during and after the clinical study for monitoring, audits, EC review and regulatory authority inspections.

### **9.1 Data Management Plan**

A detailed data management plan (DMP) will be established to ensure consistency of the collected data. This document will include procedures used for data review, database cleaning, and issuing and resolving data queries. If appropriate, the DMP may be updated throughout the study duration. All revisions will be tracked and document controlled.

Electronic CRF data will be captured in a validated electronic database management Oracle Clinical system hosted by SJM. Only authorized site personnel will be permitted to enter the data through the electronic data capture (EDC) system deployed by SJM. An electronic audit trail will be used to track any subsequent changes of the entered data.

### **9.2 Document and Data Control**

#### **9.2.1 Document and data traceability**

The investigator will ensure accuracy, completeness, legibility and timeliness of the data reported to the Sponsor on the eCRFs and in all required reports.

#### **9.2.2 Recording data**

Source documents will be created and maintained by the investigational site throughout the clinical study. Data reported on the eCRFs will be derived from, and be consistent with, these source documents, and any discrepancies will be explained in writing.

The eCRFs will be signed and dated (validated eCRF) by the authorized site personnel, as specified in the Data Management Plan.

## **10. MONITORING**

It is the responsibility of SJM as the Sponsor of the study to ensure the study is conducted, recorded, and reported according to the approved protocol, subsequent amendment(s), applicable regulations, and guidance documents. Monitoring will be conducted according to the SJM Clinical Monitoring standard operating procedure.

Centralized monitoring will occur through routine internal data review. This monitoring is designed to identify missing and inconsistent data, data outliers, and potential protocol deviations that may be indicative of site non-compliance. On-site monitoring may occur at the discretion of the Sponsor if significant concerns arise. The investigator shall make subject and study records available to the clinical monitor for monitoring.

## **11. REGULATORY INSPECTIONS**

The investigator and/or delegate should contact SJM immediately upon notification of a governmental agency inspection at the site. A clinical monitor or designee will assist the investigator and/or delegate in preparing for the audit.

An investigator, or any person acting on behalf of such a person with respect to the study, will permit authorized governmental agency employees, at reasonable times and in reasonable manner, to inspect and copy all records relating to the study.

An investigator will permit authorized governmental agency employees to inspect and copy records that identify subjects, upon notice that governmental agency has reason to suspect that adequate informed consent was not obtained, or that reports required to be submitted by the investigator, to the Sponsor or EC have not been submitted or are incomplete, inaccurate, false or misleading.

## **12. STATISTICAL METHODS**

No formal hypothesis will be tested for this observational post-market study. However, point estimates and exact 95% confidence intervals will be provided for the following rates in the study:

- Procedural serious adverse events (0 - 7 days) post procedure or before hospital discharge whichever latest) will be summarized for all subjects as well as stratified by imaging modality used for implanting the device (TOE and ICE)
- Late serious adverse events through 2 years
- Occurrence of ischemic stroke , systemic embolism and cardiovascular death through 2 years
- Occurrence of bleeding (including hemorrhagic stroke) events through 2 years

Data collected on the following objectives will also be reported:

- Technical success (secondary objective)
- Procedural success (secondary objective) - This objective will be summarized for all subjects as well as stratified by imaging modality used for placement of the device (TOE and ICE)
- OAC usage through 2 years (secondary objective)

- Serious Adverse Events – this may include, but is not limited to:
  - Significant bleeding events (e.g. cardiac tamponade, central nervous system (CNS) bleeding, and any bleeding related to the device or procedure that necessitates an operation)
  - Endocarditis
  - Device embolization (summarized by those that can be snared, and those that require surgical intervention)
  - Thrombus on device
  - All strokes
  - Transient ischemic attacks
  - Systemic embolism
  - Cardiovascular death
- Closure at procedure and 1-3 months post implant
  - The echo core lab's adjudication of residual flow will be used for this analysis. The following guidelines will be used:
    - None – No color flow jet in or out of the LAA
    - Small leak: < 3 mm diameter jet by color flow Doppler
    - Medium leak: 3-5 mm diameter by color flow Doppler
    - Large leak: > 5 mm diameter jet by color flow Doppler

Other variables may be summarized as deemed appropriate. The numerator for all rates will be the number of subjects who experience the corresponding event. The denominator for all rates will be subjects who experience the corresponding event plus all other subjects who achieve 2-years of follow-up.

Version 9.0 or higher of the SAS® statistical software package or other widely accepted statistical software will be used to provide all statistical analyses. Unless otherwise stated, attempts will not be made to adjust for multiple comparisons.

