## **8. SERIOUS ADVERSE EVENTS, SERIOUS ADVERSE DEVICE EFFECTS, DEATHS AND DEVICE DEFICIENCIES**

Risks associated with the Amulet device are similar to other implantable cardiac occlusion devices. Some of the potential risks include but are not limited to those listed below. The definitions noted below are used for the purposes of this study. Radiation risks associated with the procedure are comparable to a diagnostic catheterization procedure.

Only serious adverse events (SAEs) will be collected for this study. Serious adverse events are classified as serious adverse events or serious adverse device effects (SADEs). A planned hospitalization for a pre-existing condition is not considered a serious adverse event.

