### **13.2 Clinical Events Committee**

The clinical events committee (CEC) is an independent physician group that will review and adjudicate serious adverse events that occur over the course of the study. The CEC members will not be site investigators in the study. Responsibilities and membership of the CEC will be described in a CEC charter. Board membership may include cardiologists, electrophysiologists, neurologists and neuroradiologists.

The primary responsibilities of the CEC over the course of the study are to review and refine serious adverse event definitions, and to review and adjudicate serious adverse events.

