#### **IV. Technical Notes for Completion of Echocardiographic Studies**

- a. Study subjects are to be identified only by study site and study subject number. This information will be entered in the ultrasound system patient data section in adherence to applicable privacy laws. No subject names should be displayed in the submitted studies.
- b. Two-dimensional imaging to be performed in harmonic mode; the ECG tracing should be displayed on all images (still frames and cine-loops), clearly showing P wave/QRS morphology during the echocardiographic study. Avoid recording extra systolic (PVC) beats.
- c. For all spectral Doppler velocities, please use a display speed of 100 mm/sec, and optimize the velocity profile by moving the baseline up or down and showing the maximal velocity obtained at the top of the scale.
- d. Clinical sites should retain a digital copy of the echocardiographic study in DICOM and the study should be analyzed locally. The Echocardiography Core Laboratory WILL NOT return submitted studies. An echocardiographic analysis WILL NOT be provided by the Echocardiography Core Laboratory to the clinical sites. The Echocardiography Core Laboratory Report will only be used for the purposes of the Amulet study and NOT for diagnosis and/or clinical management of subjects enrolled in the Amulet study.

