#### **VI. Measurements to be analyzed by the Echocardiography Core Lab**

- a. Thrombus in the LA and/or LAA
- b. LAA ostium measurements
- c. Length distal to the LAA ostium
- d. Thrombus in the RA and/or RAA
- e. Spontaneous Echo Contrast (SEC) in the LA
- f. Presence, location and size of any aortic plaque
- g. LAA-LA communication/flow (see VII below)

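### Device thrombus is counted from site-recorded SAEs over two-year completers, although the only scheduled TOE after implant is at 1-3 months, so the figure cannot be read as a two-year rate

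*Protocol*

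**What the plan says.** **Source.** Section 12 assigns the closure analysis at procedure and at 1-3 months to the core laboratory: "The echo core lab's adjudication of residual flow will be used for this analysis". It lists "Thrombus on device" under serious adverse events and names no source for it. Section 8.1.2 puts event recording with the sites: "Investigators will record all serious adverse events, serious adverse device effects, and deaths on the appropriate eCRF". The CEC (Section 13.2) is to "review and adjudicate serious adverse events that occur over the course of the study".

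**Recording.** Section 8 opens with "Only serious adverse events (SAEs) will be collected for this study". The thrombus paragraph in Section 8.1 says "If a thrombus is detected post- procedure, complete an Adverse Event eCRF", with no condition on symptoms or seriousness.

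**Core laboratory.** Section 13.3 has it analyse every TOE. Appendix E VI includes "Thrombus in the LA and/or LAA" but no item for thrombus on the device. Appendix E IV adds "An echocardiographic analysis WILL NOT be provided by the Echocardiography Core Laboratory to the clinical sites", and says that sites should read the study themselves.

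**Imaging.** In Table 2, the only scheduled TOE after the procedure is at 1-3 months. The 6- and 24-month contacts are by telephone, and the 12-month visit has no TOE. At interim visits, a TOE is required if a stroke or TIA is confirmed.

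**Denominator.** Section 12 sets one rule for all rates: subjects with the event plus every other subject who reaches two years.

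**The concern.** Thrombus on the device is an imaging finding, and it is looked for on schedule only once after implant. A frequency for it should rest on the subjects who were imaged. The Section 12 rule rests on follow-up to two years instead, which is a different set of subjects. Someone who skipped the 1-3 month TOE but answered the 24-month call counts as free of thrombus. Someone with a clean TOE who left at month 18 is not counted.

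The numerator has its own weaknesses. It depends on each site's reading and on which of two recording rules the site follows. An independent reading of the same images exists, but no stated step turns a thrombus found only there into a counted event.

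The recording conflict also reaches a primary objective. A thrombus found at the 1-3 month TOE falls after day 7, so a site's view of whether it is serious helps decide whether the subject enters the late-SAE total, which is reported with an exact 95% confidence interval.

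**Working it through.** The protocol gives no thrombus rate and derives no sample size from one, so there is no figure to reproduce. Only N = 1000, the visit schedule and the denominator rule come from the protocol. Prevalence, TOE completion, site detection and attrition are assumptions.

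**1. Time without scheduled TOE.** The last scheduled TOE is at month 1 to 3. That leaves 24 − 3 = 21 to 24 − 1 = 23 of 24 months, or 87.5% to 95.8%.

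**2. The Section 12 rate as a formula.**
- Events = N × prevalence at the TOE × TOE completion × site detection relative to the core laboratory.
- Denominator = events + (N − events) × (1 − attrition).
- Rate = events / denominator.

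**3. Each part alone, with true prevalence 2%.**
- Missing TOEs (completion 70%, full detection, no attrition): 1000 × 0.02 × 0.7 = 14 events, and 14/1000 = 1.4%, which is 0.70 of the truth. Over the 700 subjects imaged, 14/700 = 2.0%.
- Attrition (30%, all imaged, full detection): 20/(20 + 980 × 0.7) = 20/706 = 2.83%, which is 1.42 times the truth. Over the 1000 imaged, 20/1000 = 2.0%.
- Site detection (60%, all imaged, no attrition): 12/1000 = 1.2%, which is 0.60 of the truth.

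The first two errors come from the denominator rule and pull in opposite directions. The third comes from the source.

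**4. Combined.** Completion 70% to 90%, site detection 60% to 100%, attrition 10% to 30%, prevalence 2% at the TOE:
- Lowest: 1000 × 0.02 × 0.7 × 0.6 = 8.4 events; denominator 8.4 + 991.6 × 0.9 = 900.8; rate 0.93%.
- Highest: 1000 × 0.02 × 0.9 × 1.0 = 18 events; denominator 18 + 982 × 0.7 = 705.4; rate 2.55%.

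| Assumed further silent thrombus after month 3, not imaged | True two-year frequency | Reported / true |
|---|---|---|
| none | 2% | 0.47 to 1.28 |
| 1% | 3% | 0.31 to 0.85 |
| 2% | 4% | 0.23 to 0.64 |

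**5. Sampling error for comparison.** The exact 95% interval for 20 of 1000 is 1.23% to 3.07%. It allows for none of the errors above.

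**6. Missed cases at the TOE.** If prevalence is 2% to 4% and sites miss 10% to 30%, the loss is 1000 × 0.02 × 0.10 = 2 to 1000 × 0.04 × 0.30 = 12 cases.

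**7. Late-SAE total.** At the same 2% to 4%, 20 to 40 subjects per 1000 have a thrombus at the TOE. That is the most that could enter or leave the total on the recording rule alone. Subjects who have another late SAE, or whose thrombus is serious on any reading, do not move.

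**The case against.** The strongest reply is that the protocol captures more than a quick reading suggests, and four parts of it stand.

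- A reader might infer that silent thrombus goes unrecorded. It does not follow. Sites read the TOE locally, and the thrombus paragraph asks for a form for any thrombus detected. A treated thrombus may also meet the SAE definition through its limb on intervention, or the wider serious-adverse-device-effect definition in Section 8.1.1. What can be lost is thrombus seen only by the core laboratory, cases a site omits under the SAE-only rule, and silent thrombus with no later imaging.
- A reader might infer that late thrombus is found only after a stroke or TIA. That is the only later TOE the protocol requires, but Section 6.2 also expects standard-of-care echocardiography for thrombus formation, and unscheduled visits are allowed. Neither is standardised.
- A reader might infer that the rate is understated, or that its link with stroke is exaggerated. The completer denominator can push the rate up, and no thrombus-stroke analysis is planned.
- Section 12 does not itself label thrombus as a two-year outcome. That meaning comes only from the denominator rule.

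It can also be said that a statistical analysis plan, data management plan or CEC charter could name the source and the reconciliation step, and that Appendix E IV permits study use of core-laboratory reports. That is fair on the source, where Section 12 is silent rather than exclusionary. It does not answer the rest. Section 12 itself fixes the denominator, an analysis plan cannot settle two conflicting recording rules at up to 75 sites, and it cannot add an item to readings already made. On the core-laboratory list, thrombus in the left atrium or appendage covers the region where the device sits, so a named item is a refinement.

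**Conclusion.** The concern holds in a limited form. Under the Section 12 rule, the device-thrombus figure is neither a prevalence among imaged subjects nor a two-year cumulative rate. Unimaged completers count as negative, imaged negatives who leave early are dropped, and core-laboratory-only findings have no stated route in. Section 8 also contradicts itself on whether a non-serious thrombus is collected, which can make site reporting and the late-SAE total vary.

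The direction of the bias is not established. Under the assumptions shown, the ratio of reported to true is 0.47 to 1.28 if no thrombus arises after the TOE, and it falls below 1 throughout that grid only if silent thrombus arises later. The loss of 2 to 12 cases per 1000 is illustrative. Thrombus is not a named primary or secondary objective, so the point reaches a primary objective only through late SAEs. The change should be made because it is cheap and gives the figure a clear meaning.

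**What to change.** 1. In Section 12, report device thrombus as core-laboratory prevalence at the 1-3 month TOE, over subjects with an evaluable TOE, with an exact 95% interval and next to closure. Give the number without an evaluable TOE. Report later thrombus separately as clinically detected, not as a two-year rate.
2. In Appendix E VI, add thrombus on the device, coded present, absent or not evaluable.
3. Reconcile the opening of Section 8 with the thrombus paragraph in Section 8.1, so that one rule says whether every post-procedure thrombus is recorded. Keep seriousness as a separate field, so that the late-SAE total follows the SAE definition.
4. Have the sponsor list discordant core-laboratory and site readings for CEC review.

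The cost is one item on a reading already made, edits to two sections, and a reconciliation listing. It needs no extra imaging or reader. The reported thrombus rate may come out higher. The prevalence still assumes that subjects with an evaluable TOE resemble those without one, and the change does not fill the months without scheduled imaging; it stops the figure from implying that they were covered.
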